From 2021, ENT departments of the Region of Southern Denmark, and the North Denmark Region have entered the Danish tonsil database collaboration. The database contains pre-, per-, and postoperative information about tonsil surgery, including surgical method and instruments.

Although cold steel tonsillectomy is considered the gold standard surgical technique, several hot techniques including bipolar techniques, diathermy, and coblation have been developed for tonsillectomy^2^. Hitherto, these hot instruments have not proven superior to the gold standard in terms of reducing PTH, and it is recommended, that these hot techniques should be used with caution^2,3,5,8,18,19^. In cold steel tonsillectomy the peritonsillar space is dissected with metal instruments, and bleeding is typically controlled by ligation or electrocautery.

Recently, a new impedance-dependent tissue sealer (IDTS) device (BiZact^TM^) has been approved for all benign indications for tonsillectomy^20^. Preliminary results are promising in terms of a PTH rate of 4.5%, a shortened operative time with a median time of 5.1 minutes (range 1.5-26.5 minutes), and a reduced intraoperative blood loss to 1-10 milliliters^20^. With the IDTS the peritonsillar space is dissected and sealed in one step using adjustable energy from a ValleyLab FT10 Energy Platform (Medtronic) measuring the impedance of the tissue grasped with the instrument securing hemostasis before the surgeon cuts the tissue.

Ideally, if a gold standard technique is to be replaced by a new technique, it is recommended that the decision should be based on scientific studies performed as randomized designs.

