**Method**

*Design*

The project is designed as a Danish randomized controlled multi-center trial of tonsillectomy by conventional cold steel surgical technique versus IDTS. The study is blinded for patients until six months after surgery and the study is assessor blinded.

Randomization is computerized via the tonsil database and utilizes block randomization for each department in a random table of 2000 with equal numbers of group assignments. The randomization is only apparent to the surgeon on the day of the surgery and the day before.

*Course*

All elective and acute patients referred to tonsillectomy, with or without adenoidectomy, on benign indications will be assessed for eligibility at the participating ENT departments. Given a signed declaration of consent patients will be enrolled and randomized in the study to either the standard cold steel tonsillectomy or to IDTS tonsillectomy.

After surgery all patients will be brought to the recovery room for 1-4 hours or hospitalized for a day. Before hospital discharge a surgeon will check for postoperative hemorrhaging and the patient and caregivers will receive oral and written recommendations for the postoperative period. Patients or caregivers are requested to follow the recommendations, and they are instructed to contact the ENT department or to call an ambulance, if postoperative hemorrhage occurs.

There will be no planned postoperative visits at the hospital. During the first six postoperative months included patients/caregivers are asked to complete electronic questionnaires online on their mobile device: daily, for the first two postoperative weeks, and again one month and six months postoperatively.

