**Outcome Assessment**

Primary endpoints:

- Incidence of PTH defined as hemorrhage requiring hemostasis with bipolar electric coagulation, ligature, compression and/or medical treatment with anti-fibrinolytic within the first 24 hours after surgery (early PTH) until 30 days after surgery (late PTH).
- Intraoperative blood loss assessed by a standardized protocol utilizing the gravimetric method. The nurse suctions up 100 ml of NaCl weighed on the scale for precision (Kern & Sohn, PCB 6000-1). The suction canister is also weighed on the scale, as well as the dry gauze. After the surgery the canister of blood including the NaCl is weighed and the dry weights of the canister and gauze including the NaCl are subtracted, this leaves the total blood loss of the operation. It is assumed that 1 gram blood = 1 ml blood.
- Operative time in minutes from the Boyle-Davis gag is placed until it is removed. The operating nurse is responsible for measurements of time.
- Postoperative pain is assessed on an 11-point numeric rating scale ranging from 0 “no pain” to 10 “worst possible pain”. For children, the Wong-Baker Faces rating scale will be used.

Secondary endpoints:

- Patient reported: Unscheduled contacts to the health care system, patient satisfaction, health related quality of life, and patient reported quality of smell and taste via a validated TASTE questionnaire, followed by further investigation should the patient report altered taste at six months.

Variables:

- Patient reported outcome measures (PROMs) of postoperative recovery (return to normal diet, physical activity, and return to work, school, or childcare), compliance to postoperative recommendations.

**Inclusion criteria:** First time tonsillectomy due to; Tonsillar hypertrophy, recurrent tonsillitis (including previous peritonsillar abscess), chronic tonsillitis, systemic complications to tonsillitis, other (mononucleosis), PFAPA (periodic fever, aphthous stomatitis, pharyngitis, cervical adenitis), tonsillar plugs, peritonsillar abscess and signed written consent.

**Exclusion criteria:** Diseases in the hematopoietic system, antithrombotic or anticoagulant drugs in the recovery period, suspicion of or known malignancy, patients, or parents unable to read or speak Danish, patients, or parents unable to use online application for self-evaluation, patients or parents unable to give informed consent, body weight under 16 kilograms.

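### Peritonsillar abscess is an eligible indication, but the gravimetric rule records any abscess content collected as blood loss, a listed primary endpoint

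*Protocol*

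**What the plan says.** Under Outcome Assessment, the inclusion criteria name the abscess twice. It appears once as history, in "recurrent tonsillitis (including previous peritonsillar abscess", and once as an item of its own at the end of the list, in "tonsillar plugs, peritonsillar abscess and signed written consent". The Course paragraph of the Method section opens recruitment to "All elective and acute patients referred to tonsillectomy, with or without adenoidectomy, on benign indications".

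Blood loss is the second of four primary endpoints: "Intraoperative blood loss assessed by a standardized protocol utilizing the gravimetric method". The nurse suctions a weighed 100 ml of NaCl, and canister and dry gauze are weighed too. After surgery, "the dry weights of the canister and gauze including the NaCl are subtracted", and "this leaves the total blood loss of the operation. It is assumed that 1 gram blood = 1 ml blood".

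The Introduction gives the only indication of scale. It cites preliminary results for the device with "a reduced intraoperative blood loss to 1-10 milliliters".

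Statistical analysis assigns continuous data to a t-test or a Mann-Whitney test and follows intention to treat. It names surgical indication among the confounders for a multiple logistic regression. It also promises stratification without naming the strata.

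**The concern.** The rule suits an operation in which the only fluids collected are saline and blood. It does not suit an operation on a patient with an abscess present, which the inclusion list appears to admit deliberately. Abscess content that reaches the canister or the gauze adds weight, nothing deducts that weight, and the rule converts it to millilitres of blood.

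This has to be settled in the protocol because it is a procedure carried out in theatre. Once the fluids share a canister, no statistical method recovers the blood volume. At stake are the accuracy of values in one patient group, the absolute volumes reported for each technique, and some precision. The volumes cited for the device are small enough for a few millilitres to matter in a single patient.

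**Working it through.** **1. The rule as arithmetic.** Recorded loss = final weight − dry canister − dry gauze − NaCl = blood + any other fluid collected. The protocol text contains no deduction, second canister, flag or exemption for abscess content.

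**2. Is a current abscess meant?** The word acute does not stand beside the abscess item. Previous abscess is already covered under recurrent tonsillitis, so the separate item would be redundant unless it meant a current abscess. The admission of acute patients points the same way. This is an inference, but a sound one.

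**3. Inputs.** The protocol states no figure for abscess share, abscess volume or the SD of blood loss, so there is nothing of its own to reproduce. Assumed here: share f = 5-30%, collected volume V = 5-15 ml per abscess patient, true SD = 5-20 ml, and V independent of true blood loss. From Power Considerations: 1126 patients before dropout, or 563 per arm.

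**4. Single patient.** With 5 ml true loss and 10 ml abscess content, 15 ml is recorded, three times the truth.

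**5. Arm level, with V the same in every abscess patient.**
- Rise in the arm mean = f·V
- Added variance = f(1−f)V²
- Standard error of chance imbalance between arms = √(2·f(1−f)V²/563)

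| f | V (ml) | Rise in mean (ml) | Added variance (ml²) | SE of imbalance (ml) |
|---|---|---|---|---|
| 5% | 5 | 0.25 | 1.19 | 0.07 |
| 10% | 5 | 0.50 | 2.25 | 0.09 |
| 20% | 10 | 2.00 | 16.00 | 0.24 |
| 30% | 15 | 4.50 | 47.25 | 0.41 |

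If V varies between patients with an SD of half its mean, the added variance becomes f(V/2)² + f(1−f)V². For 5% and 5 ml this is 0.3125 + 1.1875 = 1.5. For 20% and 10 ml it is 5 + 16 = 21, with an imbalance SE of √(2·21/563) = 0.27 ml.

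**6. Loss of precision** = added variance / SD².
- 10%, 5 ml, SD 20: 2.25/400 = 0.6%.
- 30%, 15 ml, SD 20: 47.25/400 = 12%.
- 30%, 15 ml, SD 10: 47.25/100 = 47%.
- 20%, 10 ml, varying V, SD 20: 21/400 = 5%.
- 20%, 10 ml, varying V, SD 5: 21/25 = 84%.

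**7. What that does to the comparison.** At 563 per arm, two-sided 0.05 and 80% power, the detectable difference with SD 10 is 2.80·√(2·100/563) = 1.7 ml. With 47% more variance it is 1.7·√1.47 ≈ 2.0 ml.

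**The case against.** The strongest reply is that the endpoint is compared as a difference between arms. Indication precedes randomization, so the same offset is expected on both sides and cancels from the difference in means. This stands, provided the instrument does not change how much abscess content is collected. A reader might infer that the rule favors one technique, or that blocking by department alone lets an imbalance in abscess cases distort the result. The documents do not support either. The imbalance has a standard error of at most 0.41 ml on the fixed-volume inputs, and it is ordinary sampling error already reflected in the test.

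A reader might also infer that a relative reduction would be seriously diluted. The protocol plans differences, not ratios, and gives no cold-steel volume, so such dilution cannot be sized. The 1-10 ml is a pilot result, not the trial's planning assumption.

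It can further be said that every magnitude here is assumed, that the protocol may only summarize a fuller measurement procedure, and that saliva would be counted too. It is also not stated that abscess content reaches the canister. All fair, and these points limit the severity. They do not answer the text as written, under which whatever is collected counts as blood. Unlike saliva, abscess content is confined to a patient group identifiable in advance.

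Naming surgical indication as a confounder is not a repair. The named model is logistic and the endpoint is a volume. Stratification by indication, if that is what is intended, would help the comparison but leave the recorded values wrong.

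**Conclusion.** The point holds as a measurement flaw of moderate importance. It is not a bias between arms. Under the protocol's rule, abscess content collected during surgery is recorded as blood in a primary endpoint. Individual values can be wrong by an amount comparable to the whole range cited for the device. Arm means rise by about 0.25-4.5 ml under the assumed shares and volumes.

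The added noise is modest over most of the assumed range. The 47% figure needs the highest share, the highest volume and an SD of 10 ml together. Larger losses of precision arise only if the true SD is as small as about 5 ml, or if the collected volume also varies widely in that worst corner. With SD 10 ml the detectable difference moves only from about 1.7 to 2.0 ml, even with 47% more variance.

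The conclusion rests on reading the separate abscess item as a current abscess, and on some of its content reaching the canister or gauze. The sample size, which is based on hemorrhage, is unaffected, as are the hemorrhage, pain and operative-time endpoints.

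**What to change.** In the blood-loss procedure under Outcome Assessment, state that abscess content is collected in a separate tared canister where feasible and not counted. State also that a value is flagged in the database when separation was not possible.

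In Statistical analysis, keep all randomized patients as the main blood-loss comparison. Adjust or stratify it by the recorded abscess indication, using a model suited to a continuous outcome. Report patients without the abscess indication, as recorded before randomization, as a sensitivity analysis. Making that subgroup the main comparison would conflict with the protocol's intention-to-treat commitment and discard randomized patients in order to remove an offset expected to be equal in both arms.

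The cost is an occasional extra canister, one database field and a few sentences of protocol text.

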**Power Considerations:** The sample size calculation is based on data from the Danish Tonsil Database. In a twelve months period, the frequency of PTH causing reoperation with hemostasis was 7.9%. With an expected non-inferiority treatment difference between the IDTS and the cold steel instrument, a significance level of 0.05, a power of 80%, and a non-inferiority limit of 4%, the required sample is 1126 patients. Assuming a drop out frequency of 10% into account, a total of 1250 patients are required. With a non-inferiority limit set to 4%, the present study will be able to detect a clinically relevant change in the frequency of PTH causing reoperation with hemostasis.

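### The sample size and the 80% power claim rest on reoperation for hemorrhage (7.9%), but the primary endpoint is a wider event for which no rate is given, so the stated power is not supported for that endpoint

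*Protocol*

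**What the plan says.** **Endpoint.** The first primary endpoint under Outcome Assessment is the incidence of PTH, defined as "hemorrhage requiring hemostasis with bipolar electric coagulation, ligature, compression and/or medical treatment with anti-fibrinolytic". It covers early bleeds (first 24 hours) and late bleeds, "until 30 days after surgery (late PTH"). The and/or means that any one listed measure is enough. Return to the operating theatre is not part of the definition.

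**Sizing.** Power Considerations says "The sample size calculation is based on data from the Danish Tonsil Database", and that over twelve months "the frequency of PTH causing reoperation with hemostasis was 7.9"%. The other inputs are "a significance level of 0.05", 80% power and "a non-inferiority limit of 4"%. They give 1126 patients, raised to 1250 for 10% dropout. The section closes by naming reoperation PTH again as the outcome in which the trial can detect a clinically relevant change.

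**What is not stated.** No rate is given for the wider definition, and no sentence links the two events. The 7.9% is not said to be a cold-steel rate, a rate in patients who would meet the trial's eligibility criteria, or a 30-day rate.

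**The concern.** PTH is the only one of the four primary endpoints with a power calculation, so this is the protocol's only stated power claim. It is made for a different event from the one that will be analysed.

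Two things are at stake. The first is power. If a bleed that leads to reoperation with hemostasis is stopped by one of the listed means, it is also a primary event, whereas a bleed managed by compression or a drug alone is a primary event but not a reoperation. Within one population and time window the wider rate therefore cannot be lower, and it is higher as soon as one patient is managed without reoperation. At rates in this region the binomial variance rises with the rate, so a fixed 4-point absolute margin becomes harder to meet. The second is the margin. The protocol calls 4 points clinically relevant for reoperation PTH only, and nothing in it supports the same margin for an event that mixes reoperations with bleeds treated conservatively.

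**Working it through.** **Inputs**

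- Common rate p = 7.9% (Power Considerations).
- Margin 0.04, power 80%, significance level 0.05 (Power Considerations).
- 1:1 allocation (Design).
- Two inputs are not given as numbers. The true difference is described only as "With an expected non-inferiority treatment difference between the IDTS and the cold steel instrument", and the sidedness of the 0.05 is not stated. A difference of 0 and a one-sided 0.05 are assumed because together they return the stated sample size.

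**Step 1: reproduce the plan's figure**

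n per arm = 2p(1−p)(z₀.₉₅ + z₀.₈₀)² / margin²

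- 2 × 0.079 × 0.921 = 0.145518
- (1.645 + 0.842)² ≈ 6.183
- n = 0.145518 × 6.183 / 0.0016 ≈ 562.3, rounded up to 563 per arm, **1126 in total**

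This matches exactly. Dropout: 1126 / 0.9 ≈ 1251, in line with the stated 1250. The sample size therefore uses the reoperation rate with no allowance for the wider event.

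**Step 2: power at other common rates**

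Power = Φ(0.04 / √(2p(1−p)/n) − 1.645)

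For example, at p = 10% and n = 563: √(0.18/563) = 0.01788; 0.04/0.01788 = 2.237; 2.237 − 1.645 = 0.592; Φ(0.592) = 72.3%.

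The rates above 7.9% are assumptions. The last column is the evaluable total from the Step 1 formula.

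| Rate in both arms | Power, 1126 evaluable (563 per arm) | Power, all 1250 analysed (625 per arm) | Evaluable total for 80% |
|---|---|---|---|
| 7.9% (protocol) | 80.0% | 83.6% | 1126 |
| 8.5% | 77.7% | 81.3% | 1204 |
| 10% | 72.3% | 76.2% | 1392 |
| 12% | 66.3% | 70.2% | 1634 |

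**Step 3: how much room the dropout allowance gives**

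The Statistical analysis section plans an intention-to-treat analysis of all randomized patients. If PTH is known for all 1250, the same formula with n = 625 gives 80.3% at 8.8% and 79.6% at 9%, so 80% holds up to a rate of about 8.8%.

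**The case against.** The strongest objection concerns the step from a wider definition to a higher rate in this trial. A reader might infer that the control rate will exceed 7.9% and that the trial is underpowered. The documents do not support that. The ordering of the two rates holds only within the same population and window. The 7.9% comes from a database that, according to the Introduction, records surgical method and instruments, and it is not said to be restricted to cold steel. The trial excludes hematopoietic disease and antithrombotic or anticoagulant drugs in the recovery period. The trial's cold-steel rate on the wider definition could lie above, near or below 7.9%. This stands, and it limits the conclusion.

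Other parts of the objection also stand:

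- **Dropout allowance.** If outcomes are complete, it absorbs a modest rise in the rate (Step 3).
- **True difference.** The losses assume none. At 10% with cold steel and 9.5% with the tissue sealer, power with 563 per arm is Φ(0.045 / √((0.10 × 0.90 + 0.095 × 0.905)/563) − 1.645) = 81.6%. A difference in the other direction would lower it further.
- **Sidedness.** At one-sided 0.025, equivalent to a two-sided 95% interval, power with 1126 patients is about 70% even at 7.9%. That loss comes from the choice of alpha, not from the endpoint, so it is not counted here.
- **Less severe components.** A reader might infer that compression and drug treatment add noise that pulls the arms together. Nothing in the protocol says that treatment thresholds vary or that these bleeds are unrelated to technique. Such noise would in any case favour a non-inferiority conclusion, which is a different issue from lost power.
- **Deliberate choice.** The Discussion explains that severity is defined by the intervention needed because no agreed definition exists. The wider endpoint is therefore not itself an error.

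None of this removes the mismatch. The endpoint and the basis for its sample size are both fixed in this protocol, and they name different events.

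**Conclusion.** The point holds as a mismatch. The 80% power is reproduced for reoperation PTH at 7.9% and is not supported for the primary endpoint as defined. It is not shown that the trial is underpowered, because the wider rate is not in the documents.

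The size is conditional on equal rates in both arms, a 4-point margin and one-sided 0.05. For assumed rates of 10% to 12%, power is 72.3% to 66.3% with 1126 evaluable patients, or 76.2% to 70.2% with all 1250. A rate of 8.5% costs about 2 points with 1126 and leaves power above 80% with 1250. The direction rests on comparing the two events in the same population and window, and on hemostasis at reoperation being achieved by one of the means listed in the endpoint.

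**What to change.** Reconcile Outcome Assessment and Power Considerations so that both refer to the same event.

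1. Take the rate for the primary endpoint as defined from the Danish Tonsil Database, if it is recorded there, and say which techniques and what follow-up window it covers. If it is not recorded, state an assumed range.
2. Restate the power at that rate or range for both 1126 and 1250 patients.
3. Justify the 4-point margin for the wider event.
4. Prespecify reoperation PTH within 30 days, the event used for sizing, as a separate analysis. The legend to Figure 2 says that the doctor enters a detailed account of each hemorrhage, so trial data for this should be available.

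Making reoperation PTH the primary endpoint would also align the two sections, but it would give up the definition that the Discussion argues for. It is a trade-off for the sponsor and is not needed to correct the mismatch.

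The cost is amended wording and, if available, one database query. The stated power may become less favourable. If the rate proves to be 10% to 12% and 80% is still wanted, 1392 to 1634 evaluable patients would be needed instead of 1126.

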**Statistical analysis**

Endpoints will be evaluated as differences between treatment groups. Categorical data are analyzed by chi2 or Fisher’s exact test. Depending on normal distribution, continuous data is analyzed by either un-paired Student’s *t-test* or Mann-Whitney rank sum test. An Intention-to-treat principle will be used including all randomized participants in the analysis. Stratification will be performed, and confounding factors (sex, age, surgical indication, BMI, smoking, comorbidity) analyzed in a multiple logistic regression model. Repeated measurement data will be analyzed in a mixed effect model for repeated measurements (ANOVA) with group and time as systematic factors and patients as random effect. The model takes random variations over time into account. Post-hoc tests will be based on the Kenward-Roger approximation to test all included patients despite missing data. The significance level is set at 0.05.

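### The sample size of 1126 matches an unstated one-sided 0.05 level; if non-inferiority is judged by a 95% confidence interval, power is about 70%, not 80%

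*Protocol*

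**What the plan says.** Under Power Considerations, the protocol takes its event rate from the Danish Tonsil Database, where "the frequency of PTH causing reoperation with hemostasis was 7.9" per cent over twelve months. It then gives "a significance level of 0.05, a power of 80%, and a non-inferiority limit of 4%, the required sample is 1126 patients", raised to 1250 for 10% dropout. On the true difference it says only "With an expected non-inferiority treatment difference between the IDTS and the cold steel instrument", with no figure. It does not say whether 0.05 is one-sided or two-sided.

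Under Statistical analysis, endpoints are evaluated as differences between groups. "Categorical data are analyzed by chi2" or Fisher's exact test, and continuous data by the t-test or Mann-Whitney test. One level covers everything: "The significance level is set at 0.05". The section names no one-sided test, no confidence interval and no separate level for the non-inferiority comparison. The primary objective is non-inferiority of IDTS to cold steel on post-tonsillectomy hemorrhage (PTH) and pain.

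**The concern.** A non-inferiority conclusion depends on one confidence limit, so its error rate is one-sided. A bare level of 0.05 can then mean two things. One is a one-sided 0.05 test, equivalent to using the upper limit of a two-sided 90% interval. The other is a two-sided 0.05 convention, equivalent to a 95% interval and a one-sided 0.025 test. The sample size fits only the first. The tests listed for the analysis, read in the usual way, point to the second.

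Two things are at stake. The first is whether the stated 80% power belongs to the analysis that will be run. The second is the decision rule itself, because there are results that pass with a 90% interval and fail with a 95% interval. The endpoint is one that the protocol's introduction calls potentially life-threatening, so the rule should be fixed in advance.

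**Working it through.** **Inputs**
- Event rate p = 0.079, margin M = 0.04, power 80%, level 0.05: Power Considerations. The margin is taken as absolute, because that reproduces 1126.
- Allocation 1:1: Method, Design ("block randomization for each department in a random table of 2000 with equal numbers of group assignments").
- True difference 0, so 7.9% in both arms: an assumption, inferred because it reproduces 1126.

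**Reproducing the plan's figure**

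n per arm = 2p(1−p)(z₁₋α + z₀.₈₀)² / M²

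Here 2p(1−p) = 2 × 0.079 × 0.921 = 0.145518 and M² = 0.0016.

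- One-sided 0.05: (1.6449 + 0.8416)² × 0.145518 / 0.0016 = 562.3, rounded up to 563 per arm, **1126 in total**. This matches the protocol exactly.
- One-sided 0.025: (1.9600 + 0.8416)² × 0.145518 / 0.0016 ≈ 713.8, rounded up to 714 per arm, 1428 in total. This does not match.

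Other designs were tried and none gives 1126:
- Superiority, 7.9% against 3.9%: 858 to 1186, depending on sidedness and continuity correction.
- Superiority, 7.9% against 11.9%: 1378 to 1848.
- Non-inferiority with the IDTS-arm variance taken at 11.9%: 1374 or 1744.
- Equivalence: 1558 or 1912.

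For dropout, 1126 / 0.9 = 1251.1. The stated 1250 is close enough.

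**Power at each level**

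Power = Φ((M − d)/SE − z₁₋α), where d is the true IDTS rate minus the true cold-steel rate and SE is the unpooled standard error.

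With d = 0 and 563 per arm, SE = √(0.145518/563) = 0.01608 and M/SE = 2.488.
- One-sided 0.05: Φ(2.488 − 1.645) = 80.0%.
- One-sided 0.025: Φ(2.488 − 1.960) = 70.1%.

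With d = 0 and 625 per arm (all 1250 analysed), SE = 0.01526 and M/SE = 2.621.
- One-sided 0.05: 83.6%.
- One-sided 0.025: 74.6%.

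**Dependence on the zero difference** (563 per arm, cold steel 7.9%)

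| True IDTS rate | SE | (M − d)/SE | Power, one-sided 0.05 | Power, one-sided 0.025 |
|---|---|---|---|---|
| 8.4% | 0.01631 | 2.146 | 69.2% | 57.4% |
| 7.9% | 0.01608 | 2.488 | 80.0% | 70.1% |
| 7.4% | 0.01584 | 2.841 | 88.4% | 81.1% |
| 4.5% (pilot PTH rate, Introduction) | 0.01434 | 5.161 | above 99% | above 99% |

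**Can the level change the conclusion?**

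Take 563 per arm and 44 cold-steel events (7.8%). With 50 IDTS events the difference is 6/563 = 1.07 points, with standard error 1.65 points. The upper limit is 1.07 + 1.645 × 1.65 = 3.78 points with the 90% interval, which is inside the margin. It is 1.07 + 1.96 × 1.65 = 4.30 points with the 95% interval, which is outside. The same split occurs with 49 or 51 IDTS events.

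**The case against.** The strongest reply is that the protocol contains no error. Neither sidedness nor any confidence interval is mentioned anywhere in it. A margin test is one-sided by nature, so 0.05 can coherently be read as one-sided throughout, and the stated inputs then give exactly 1126. The chi-square, Fisher, t and Mann-Whitney tests are listed generically for all endpoints. They test for a difference and do not use the 4-point margin, so their usual two-sidedness does not settle the level of the non-inferiority comparison. Details of this kind are also often completed in a statistical analysis plan, which may exist. Finally, the shortfall depends on a true difference of exactly zero, and a half-point advantage for IDTS brings power back above 80% even with a 95% interval.

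Most of this stands. A reader might infer that the protocol commits to a 95% interval and that its 80% is therefore wrong, or that 1126 was miscalculated. The document supports neither: the two-sided reading is an inference from convention, and the arithmetic is right under a one-sided 0.05 level. It also does not say that the level will be chosen after the data are seen.

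The reply does not remove the ambiguity. The protocol states its level twice without qualification, and its sample size holds under only one meaning of it. A later plan could choose the 95% interval, but the 80% in the protocol would not then apply. The dependence on the true difference also works in both directions: at an IDTS rate of 8.4%, power with a 95% interval falls to 57%. The sponsor's own figure of 1126 corresponds to equal rates.

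**Conclusion.** The point holds conditionally. The sample size rests on a one-sided 0.05 level and a zero true difference, neither of which the protocol states. If non-inferiority is judged at the ordinary two-sided 0.05 level of the listed tests, power is 70.1% with 1126 evaluable patients and 74.6% with all 1250, about 10 and 5 points below the stated 80%. If one-sided 0.05 is intended, the 80% stands and only the wording is incomplete; the trial then accepts a 5% risk of passing a technique whose true excess is exactly at the margin.

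These figures assume 1:1 allocation, an absolute margin, the normal approximation, a 7.9% rate in both arms, and that this planning rate applies to the endpoint tested. The match to 1126 is exact, so confidence in the calculation is high. Confidence that a 95% interval is intended is lower.

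A reader might also infer that the trial must enrol more patients. That does not follow: 1428 evaluable patients would be needed only if both the 95% interval and 80% power were to be kept at zero difference. The point should be fixed, but it is not a fatal flaw.

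**What to change.** Before outcomes by arm are seen, state the same level for the non-inferiority comparison in both Power Considerations and Statistical analysis. Either option is consistent:

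1. Non-inferiority is tested at one-sided 0.05, comparing the upper limit of the two-sided 90% confidence interval for the difference with the 4-point margin. The 1126 and the 80% stay as they are.
2. The two-sided 95% interval is used. Power is restated as about 70% with 1126 evaluable patients and 75% with 1250.

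In both cases, add to Power Considerations that 7.9% is assumed in both arms with a true difference of zero. The cost is a sentence in each section. The first option makes a 5% one-sided risk explicit; the second accepts a less favourable stated power. Enrolment does not change.

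### The power paragraph presents a non-inferiority sample size as an ability to detect a relevant change in PTH; 1126 patients give 80% power only to exclude a 4-point excess when the arms are truly equal

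*Protocol*

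**What the plan says.** The Power Considerations paragraph of the protocol takes its reference rate from the Danish Tonsil Database, where "the frequency of PTH causing reoperation with hemostasis was 7.9" percent over twelve months. The expected effect is described only in words ("With an expected non-inferiority treatment difference between the IDTS and the cold steel instrument"), with no number attached. The paragraph then gives 0.05 as the significance level, followed by "a power of 80%, and a non-inferiority limit of 4%, the required sample is 1126 patients", which becomes 1250 after a 10% allowance for dropout. It closes by tying a further property to the 4% limit: "the present study will be able to detect a clinically relevant change in the frequency of PTH causing reoperation with hemostasis".

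The Statistical analysis section says that endpoints will be evaluated as differences between the groups. For categorical endpoints it states: "Categorical data are analyzed by chi2 or Fisher’s exact test". The significance level is again 0.05. Neither section says whether tests are one-sided or two-sided, and the protocol contains no power calculation for detecting a difference.

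**The concern.** Excluding an excess and detecting a change are different properties, and they are powered under different assumptions. A non-inferiority calculation assumes a true difference, here apparently zero, and asks how often the data will rule out an excess as large as the margin. A detection calculation assumes that the change is really there and asks how often a test will find it. The closing sentence moves from the first to the second as if the margin guaranteed both.

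What is at stake is how a null result would be read. Suppose the PTH comparison were reported through a chi-square or Fisher test and came out non-significant. A reader who had been told that the study can detect a relevant change could take that result as evidence that no relevant increase exists. For a rise of the size of the margin, the planned number of patients does not support that inference.

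**Working it through.** **Inputs.** From Power Considerations: reference rate 7.9%, limit 4 percentage points, significance level 0.05, power 80%, 1126 evaluable patients and 1250 enrolled. From the Design section: equal allocation, hence 563 or 625 per arm. From Statistical analysis: chi-square or Fisher's exact test at 0.05. Two assumptions are needed. The relevant change is taken to be the 4-point limit, since the sentence names no other value. Sidedness is unstated, so both readings are shown.

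**Step 1: reproduce the protocol's own figure.** With a true difference of zero,

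n per arm = (z₁₋α + z₀.₈)² × 2p(1 − p) / margin²

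- One-sided 0.05: (1.645 + 0.842)² × 2 × 0.079 × 0.921 / 0.04² = 562.3, rounded up to 563 per arm, or 1126 in total. This is an exact match.
- One-sided 0.025: 713.8, rounded up to 714 per arm, or 1428 in total. No match.

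So 1126 is the number that excludes a 4-point excess when both arms have a true rate of 7.9%, tested one-sided at 0.05. The enrolled number is consistent with it: 1250 × 0.9 = 1125.

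**Step 2: power to detect a true 4-point rise, 7.9% to 11.9%.** The pooled rate is 0.099, and

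power = Φ{ [0.04 − z × √(2 × 0.099 × 0.901 / n)] / √[(0.079 × 0.921 + 0.119 × 0.881) / n] }

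At n = 563 the two standard errors are 0.01780 (pooled) and 0.01776 (unpooled).

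- Two-sided (z = 1.960): Φ[(0.04 − 0.03489) / 0.01776] = Φ(0.288) = 61.3%
- One-sided (z = 1.645): Φ[(0.04 − 0.02928) / 0.01776] = Φ(0.604) = 72.7%

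| Evaluable patients | Two-sided 0.05 | One-sided 0.05 |
|---|---|---|
| 1126 (563 per arm) | 61.3% | 72.7% |
| 1250 (625 per arm) | 65.9% | 76.6% |

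Exact enumeration at 563 per arm, two-sided, gives 61.8% for the uncorrected chi-square test and 57.6% with the Yates correction. A simulation of Fisher's test (4,000 trials) gave about 57%.

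**Step 3: the same question from the other side.** With 563 per arm and two-sided 0.05, the smallest rise detectable with 80% power is about 5.1 points. Detecting a 4-point rise with 80% power would need about 874 per arm, or 1748 evaluable patients.

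**Step 4: the opposite direction.** For a fall from 7.9% to 3.9% at 563 per arm, the pooled rate is 0.059 and the standard errors are 0.01404 and 0.01399. Two-sided power is Φ[(0.04 − 0.02753) / 0.01399] = Φ(0.892) = 81.4%. Both rates are lower, so the variance is smaller and the sentence holds for a fall of this size.

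**The case against.** The strongest reply is that "detect" is loose wording inside a non-inferiority argument: the authors mean that a device with a 4-point excess would not pass as non-inferior. For a non-inferiority test at one-sided 0.05 that is true, because such a device would wrongly be declared non-inferior only about 5% of the time. But failing to show non-inferiority is not the same as detecting a change. By design it also happens in 20% of trials in which the arms are identical. The test that the protocol names for categorical endpoints is a difference test, and a statistical analysis plan that specifies the non-inferiority test correctly would still leave the sentence describing the wrong property.

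Other parts of the reply stand and limit the point:

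- The protocol does not say in words that the relevant change is 4 points, nor that it would be detected with 80% power. A reader might infer both from the opening of the sentence, but they remain inferences.
- The 61% figure assumes a two-sided test, whereas the sample size implies one-sided 0.05. No single figure is settled; the fair statement is a range.
- The word used is change, and a 4-point fall is adequately covered. A reader might infer that the claim fails in both directions. It does not.
- The harmful reading arises only if the difference test drives the PTH conclusion. The objective is framed as non-inferiority, and nothing in the protocol says that a non-significant chi-square test will be taken as proof of safety.

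**Conclusion.** The point holds as a minor correction of wording. The closing sentence claims an ability that the sample size does not deliver for an increase, which is the direction the margin guards against. If the relevant change is taken as 4 points, power to detect a rise to 11.9% lies between 61% and 77% by the normal approximation for the uncorrected chi-square test, depending on sidedness and on whether 1126 or 1250 patients are evaluable. Every one of these readings is below 80%, and the Fisher or Yates-corrected version is a few points lower still in the two-sided case at 1126.

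A reader might go further and infer that the trial is too small or that 1126 is miscalculated. The documents do not support that: the number reproduces exactly on its stated inputs with a true difference of zero and one-sided 0.05, and a non-inferiority trial does not have to be powered to detect harm by a difference test. The defect is confined to the property stated in that one sentence and to what may be inferred from a non-significant difference test.

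**What to change.** Replace the closing sentence of Power Considerations with: *With 1126 evaluable patients and a true rate of 7.9% in both arms, the study has 80% power (one-sided 0.05) to exclude an increase of 4 percentage points or more.*

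Add that the conclusion on PTH rests on the confidence limit for the difference between arms, compared with the 4-point limit, and that a non-significant chi-square or Fisher test will not be taken as absence of a relevant increase. If a power for detecting a 4-point rise is quoted as well, give its sidedness and the number of evaluable patients, and show the 61–77% range rather than one figure.

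The cost is wording only. The stated capability becomes less favourable; the sample size does not change and no more patients are needed.
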